## Abstract

**Background:**

In the Netherlands, 15 % of all families with children under the age of 13 years deal with significant parenting problems. Severe parenting problems may lead to adverse physical, cognitive, and psychosocial outcomes for children, both in the short and long run. The intervention Supportive Parenting (in Dutch: “Stevig Ouderschap”) is a preventive program, which aims to reduce the risk of (developing) parenting problems among parents at risk of these problems. The intervention consists of six additional home visits by a Youth Health Care nurse during the first 18 months after childbirth and is focusing on the following elements of parental empowerment: activating social networks, increasing parenting skills and supporting parent(s)/caregiver(s) in getting grip on their own life.

**Methods and design:**

A controlled trial is performed in two regions in the Netherlands. An intervention group receives the intervention Supportive Parenting, and a control group receives ‘care-as-usual’. Parents in both the intervention and control group fill out three questionnaires focusing on various elements of empowerment (social support, parenting skills, self-sufficiency and resilience), behavioral and emotional problems of the child. The effects of the intervention will be evaluated at child age 1–3 months (baseline) and child age 18 months by comparing the outcomes between the intervention group and the control group on the primary outcomes. Additionally, interviews and focus group interviews will be held to identify factors, which hinder or stimulate a wider implementation of the intervention Supportive Parenting.

**Discussion:**

It is hypothesized that parents at increased risk of parenting problems who receive the intervention Supportive Parenting during the first 18 months after childbirth, will have enhanced their social support networks and parenting skills, increased their self-sufficiency and strengthened resilience compared to at risk parents receiving care-as-usual. Additionally children of parents from the intervention group will display less parent-reported behavioral and emotional problems.

**Trial registration:**

Netherlands Trial Register NTR5307. Registered 16 July 2015.

## Background

More than one third of Dutch parents have worried about parenting or the development of their children. More than half of these parents have sought help or advice outside their family or friends for their concerns [1]. These worries are normal and part of parenting [2].

It becomes more problematic when parents experience a discrepancy between how they would wish to raise their child(ren) and their actual parenting situation, and they do not have the means (anymore) to overcome this discrepancy (e.g. they do not know where to seek help or advice). This is what might be referred to as a parenting problem [3].

Kousemaker et al. [4] distinguishes three types of situations in which parenting problems occur, namely a mildly problematic parenting situation (i.e. parenting tasks are not always performed in an effective way and parents do not always have answers to their parenting questions), a moderately problematic parenting situation (i.e. parenting tasks are not performed in an effective way and parents do not have answers to their parenting questions) and a severely problematic parenting situation (parenting style is characterized by ineffectiveness, inconsistency, and excessive actions such as child abuse or neglect).

In the Netherlands, 15 % of all families with children under the age of 13 years deal with problematic parenting situations [1]. Of this 15 %, 10 % deals with a mildly problematic parenting situation, 4 % deals with a moderately problematic parenting situation, and 1 % deals with a severely problematic parenting situation.

A severely problematic parenting situation may lead to adverse physical, cognitive, and psychosocial outcomes for children, both in the short and long run [5–7]. Interventions can contribute to the prevention of these problematic parenting situations.

In the Netherlands, a system for monitoring children’s health and development, and for providing health promotion and disease prevention at set ages from birth onwards is available: i.e. preventive Youth Health Care. It is offered nation-wide and free of charge [8]. Participation is voluntary and the attendance rate during the first months after childbirth is about 95–100 %. During Youth Health Care visits, growth and development of the child are assessed [8, 9]. The Youth Health Care is committed to counsel parents regarding parenting skills and to promote healthy development and growth for all children [9]. Therefore, the Youth Health Care provides an opportunity to contribute to prevention, early detection, and offering interventions to parents with parenting problems.

The intervention Supportive Parenting (in Dutch: “Stevig Ouderschap”) is a theoretically well-founded intervention that aims to reduce the risk of parenting problems among parents at risk of these problems (parents with low social support, psychosocial problems, drug/alcohol use, negative feelings towards pregnancy, problematic history and/or a preterm child or child with low birthweight) [10]. Currently, 51 % of Youth Health Care centers in the Netherlands use the program [11, 12]. Supportive Parenting is based on the theories of Belsky [13–15], Newberger [16] and Baartman [17] and consists of six home visits by a Youth Health Care nurse during the first 18 months after childbirth. During the home visits the focus lies on the empowerment of parents by activating their social networks, increasing parenting skills and supporting parent(s)/caregiver(s) in getting grip on their own life.

Until now, only one study [18] has evaluated the effectiveness of Supportive Parenting on the psychosocial development of the child, parental expectations, social support, alternative punishment methods, and empathy. Bouwmeester-Landweer et al. [18] showed positive, statistically significant, effects on parental expectations and the psychosocial development of children of parents participating in the Supportive Parenting intervention. Effects of the intervention Supportive Parenting on the empowerment of parent(s)/caregiver(s) are unknown.

### Objective

A controlled trial is performed to investigate the effectiveness of the Supportive Parenting intervention in empowering parent(s)/caregiver(s) who are at risk of parenting problems in terms of social support, parenting skills, resilience, and self-sufficiency. Furthermore, we will explore which parent, child, and nurse characteristics are related to the effects of the intervention Supportive Parenting on the empowerment of parent(s)/caregiver(s) at risk of parenting problems. Additionally, interviews and focus group interviews are performed to investigate the factors that promote/hinder a broader implementation (e.g. among parents with older children [>18 months], during pregnancy, among different ethnic groups) of the intervention Supportive Parenting.

### Study hypothesis

The hypotheses of this study are that parents at increased risk of parenting problems who receive the intervention Supportive Parenting during the first 18 months after childbirth, have enhanced their social support network and parenting skills, increased self-sufficiency and strengthened resilience compared to at risk parent(s)/caregiver(s) receiving care-as-usual at child age 18 months. Additionally children from parents of the intervention group will display less parent-reported behavioral and emotional problems at child age 18 months.

## Methods and design

### Study design

A controlled trial is performed with an intervention group and a control group (‘care-as-usual’) in two regions in the Netherlands.

The inclusion of participants started shortly after childbirth. The effects of the intervention on parental empowerment and behavioral and emotional problems of the child will be evaluated at child age 1-3 months (baseline) and child age 18 months by comparing the outcomes between the intervention group and the control group.

Data collection started in January 2014 and will continue until January 2016. This study has received approval by the Medical Ethics Committee of Erasmus MC (MEC-2013-568).

### Procedure

An opportunity sample of two preventive Youth Health Care centers (CJG Rijnmond and Rivas Zorggroep) in two regions of the Netherlands participated in this study.

Nineteen of the 27 care teams of the Youth Health Care center CJG Rijnmond participated as intervention group. These locations offer the intervention Supportive Parenting to parents at risk of parenting problems as part of their regular youth health care.

The care team in the area Goerree-Overflakkee of CJG Rijnmond and all 19 preventive Youth Health Care teams of Rivas Zorggroep participated as control group. At these teams, regular youth health care is offered, the intervention Supportive Parenting is not part of this regular care. Regular care consists of the regular well-child visits at set ages.

### Participants

Between January and September 2014 parents and their children belonging to one of the participating Youth Health Care teams are eligible to participate in the study. Parents in both research groups can only participate in the study if they have at least basic Dutch language skills. The inclusion procedure of the intervention and control condition is described below. The study design and participant flow chart are shown in Fig. 1.

**Fig. 1 Fig1:**
[figure not shown]
Flow chart of the parents' participation

#### Inclusion procedure for the intervention group

As part of the regular well-child visits, a Youth Health Care nurse visits parent(s)/caregiver(s) at home 5–14 days after childbirth. During this visit the Youth Health Care nurse together with the parent(s)/caregiver(s), completes a risk assessment (the Supportive Parenting Questionnaire) to evaluate whether parent(s)/caregiver(s) are at risk of parenting problems. The risk assessment uses a score to identify parents at risk for parenting problems, Youth Health Care nurses compute this score during the visit. At-risk parents are offered the intervention Supportive Parenting.

For this study, the nurse informs these at-risk parent(s)/caregiver(s) about the study and invites parents to participate. The nurse provides the parents with an information leaflet, an informed consent form and the baseline questionnaire of the study. Parent(s)/caregiver(s) are requested to return the completed informed consent form and baseline questionnaire to the researchers in a pre-paid envelope.

#### Inclusion procedure for the control group

In the control group, as part of the regular well-child visits, a Youth Health Care nurse visits parent(s)/caregiver(s) at home 5–14 days after childbirth. The Youth Health Care nurse informs all parent(s)/caregiver(s) about the study and invites them to participate. The nurse provides parents with an information leaflet, an informed consent form and baseline questionnaire of the study. Parent(s)/caregiver(s) are requested to return the completed informed consent form and baseline questionnaire to the researchers in a pre-paid envelope.

After receiving the informed consent form and baseline questionnaire, the researchers compute the parenting problem risk score for all parents using the Supportive Parenting Questionnaire which is included in the baseline questionnaire. Parents at risk for parenting problems participate in the control group. These at risk parents in the control group receive care-as-usual. All other parents are excluded from the control group.

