### Intervention supportive parenting

The intervention Supportive Parenting aims to reduce the risk of parenting problems.

Parent(s)/caregiver(s) of newborn children, who are at risk of parenting problems, based on an assessment of risk factors through “the Supportive Parenting Questionnaire”, are offered the intervention. The Supportive Parenting Questionnaire is also based on the theories of Belsky [13–15], Newberger [16] and Baartman [17] and assesses problematic prior history of the parent(s)/caregiver(s) (experience of maltreatment in their own youth or current family; psychological disorders), risk factors of the parent(s)/caregiver(s) (drug and/or alcohol use; negative feelings towards pregnancy; age <19 years of age), risk factors of the child (preterm; low birthweight), risk factors in the social context of the parent(s)/caregiver(s) (single parent; social isolation; low spousal support) and risk factors observed by the Youth Health Care nurse. The main aim of the intervention is to increase parental awareness with regard to the impact of the factors assessed by the Supportive Parenting Questionnaire, on their current daily life and to provide parents with tools to cope with these factors.

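### The score that decides who is at risk is obtained differently in each arm of a non-randomised trial, and it is not among the named adjustment variables

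*Protocol article*

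**What the plan says.** **Intervention arm** (Inclusion procedure for the intervention group). The nurse goes through the risk questionnaire with the parent at the home visit 5–14 days after birth, and "Youth Health Care nurses compute this score during the visit". Parents found to be at risk are offered the programme. Then "the nurse informs these at-risk parent(s)/caregiver(s) about the study and invites parents to participate", and hands over the consent form and baseline questionnaire.

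**Control arm** (Inclusion procedure for the control group). At a visit in the same window, "The Youth Health Care nurse informs all parent(s)/caregiver(s) about the study and invites them to participate". The nurse hands over the forms, and "Parent(s)/caregiver(s) are requested to return the completed informed consent form and baseline questionnaire to the researchers in a pre-paid envelope". After that, "the researchers compute the parenting problem risk score for all parents using the Supportive Parenting Questionnaire which is included in the baseline questionnaire", and parents who are not at risk are excluded. Data collection describes the parents' questionnaires as self-report and dates baseline at child age 1–3 months.

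**The instrument** (Intervention supportive parenting). Besides history, parent, child and social factors, it covers "risk factors observed by the Youth Health Care nurse".

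**The analysis** (Statistical analysis). Regression on research condition, corrected where relevant for baseline measurements and for age of child and parent, parental education and ethnic background. The risk score is not named.

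**The concern.** Which parents fall in which arm follows from the care team they belong to (Procedure), so no randomisation balances the arms. The shared entry criterion is the main device that makes them comparable. If the criterion works differently in each arm, a parent could be admitted in one arm and not in the other. A parent flagged through nurse observation or something said in conversation has no described way into the control group. A parent who would disclose risk only on a private form has no way into the intervention group. If such parents differ in prognosis, the difference is added to the estimated intervention effect, in either direction, and a larger sample does not remove it.

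The order of events differs too. Intervention parents know they were flagged and offered a programme before they consent and answer the baseline questions. Control parents are scored only after doing both.

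**Working it through.** **Side by side**

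| | Intervention | Control |
|---|---|---|
| Who scores | Nurse | Researchers |
| How completed | Jointly, face to face | By the parent; form handed over by the nurse, returned by post |
| When | 5–14 days | On the baseline form, dated 1–3 months |
| Relative to consent | Before | After |
| Nurse-observed factors | In the instrument | No route into the score described |
| Who is invited | Only parents scored at risk | All parents, then screened |

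**What the planned adjustment reaches.** Baseline correction can absorb some imbalance where a baseline exists. No baseline omission is stated for the Resilience Scale, and most Parenting Stress, Family Functioning and EMPO items are asked at baseline. It cannot do so for the Parenting Stress subscale on problems with parenting or the Family Functioning parenting subscale, both left out at baseline. Nor can it for the CBCL, which is for ages 1½–5 and so has no usable baseline in newborns. For these outcomes only ages, education and ethnic background remain.

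**The plan's own power figure** (Power of the study)
- Group sizes: 313 × 0.5 = 156.5, stated as 157; 2346 × 0.5 × 0.10 = 117.3, stated as 117.
- SE of a difference in SD units: sqrt(1/157 + 1/117) = 0.122.
- Detectable difference at 80% power, two-sided 5%: (1.960 + 0.842) × 0.122 = 0.342, stated as 0.35.
- Power at 0.35: Φ(0.35/0.122 − 1.960) = 0.817, against 0.80 stated.

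Sidedness is not stated; the two-sided test matches, while one-sided gives 0.889. The figure reproduces and is not in dispute.

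**Illustration of what an imbalance would do.** Let b be the outcome difference between arms, in SD, left by the different entry scoring after adjustment. The values of b are assumptions, since the documents give none.
- False-positive rate with no true effect: 1 − Φ(1.960 − b/0.122) + Φ(−1.960 − b/0.122).
- Power at a true effect of 0.35 when b works against the intervention: Φ((0.35 − b)/0.122 − 1.960).

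| b (SD) | False-positive rate | Power at 0.35, b adverse |
|---|---|---|
| 0 | 5.0% | 81.7% |
| 0.05 | 6.9% | 69.0% |
| 0.10 | 13.0% | 53.5% |
| 0.15 | 23.3% | 37.4% |
| 0.20 | 37.4% | 23.2% |

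The SE is that of an unadjusted comparison, so the table approximates the planned regression.

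**Cost of restricting to a common cut-off** (shares assumed)
- If 20% of intervention parents fall out: 157 × 0.8 ≈ 126; 2.802 × sqrt(1/126 + 1/117) = 0.36.
- If 40% fall out: 157 × 0.6 ≈ 94; 2.802 × sqrt(1/94 + 1/117) = 0.39, with power at 0.35 of about 71%.

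**The case against.** The strongest reply is that both arms use the same named instrument and start from a nurse visit in the same window. Many of its items are largely factual and would hardly change with mode or a few weeks' delay: parental age under 19, preterm birth, low birthweight, single parenthood. The article does not say whether nurse-observed factors alone can carry a parent over the cut-off. It is also a condensed text, so silence on nurse input for controls is not proof of absence. All of this stands, and it limits how much can be claimed.

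Four stronger readings are tempting but not supported:

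- *The arms are different populations.* The documents show different operational definitions of at risk, not how far the admitted parents differ. The Discussion calls the intervention group relatively high risk, but does not compare it with the controls.
- *Nothing in the analysis deals with this.* The planned correction for baseline measurements and named confounders does so in part.
- *The false-positive rate is 37%.* That is the result for one assumed imbalance.
- *The primary comparison must be restricted to parents above a common cut-off.* Control parents who qualify only on paper would remain, so the groups would still be selected differently. The restriction would also set aside parents offered the programme in practice and cost precision.

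What the reply does not answer is that assessor, mode, order relative to consent and possibly timing differ by arm, while the score is absent from the named adjusters.

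**Conclusion.** The concern holds as a difference in how the entry score is obtained, combined with an adjustment set that does not name that score. In a non-randomised comparison this leaves a route to bias that the stated analysis closes only in part, and least for the two omitted parenting subscales and the child behaviour checklist.

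Size and direction are unknown: nurse observation could add cases in one arm, and private self-report could disclose more or less than a conversation. The range of about 7–37% for the false-positive rate rests on an assumed residual of 0.05–0.20 SD, the planned 157 and 117 parents, unit SD and an unadjusted two-sided test. It shows only that an imbalance well below the 0.35 SD target would matter.

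**What to change.** 1. Have the researchers compute one common risk score in both arms by one rule from the same parent-reported items, leaving out nurse-observed items. Use the baseline questionnaire. The article places the instrument there for controls but does not say so for intervention parents; if the items are not held there, take them from the nurse's form and note that the interview-versus-paper difference then remains.
2. Name this score as a covariate in the models under Statistical analysis.
3. Add a sensitivity analysis restricted to parents at or above the cut-off on the common score, keeping all nurse-identified intervention parents in the main analysis. Report how many intervention parents qualify only on the nurse's scoring.
4. State as a limitation that parents who would have qualified only on paper were never invited in the intervention arm, which analysis cannot repair.

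The cost is some rescoring of forms, one extra covariate and one extra analysis. The sensitivity set is less precise: the detectable difference rises from 0.34 to about 0.36 if 20% of intervention parents drop out of it, or 0.39 if 40% do.

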### Intervention supportive parenting

The intervention Supportive Parenting aims to reduce the risk of parenting problems.

Parent(s)/caregiver(s) of newborn children, who are at risk of parenting problems, based on an assessment of risk factors through “the Supportive Parenting Questionnaire”, are offered the intervention. The Supportive Parenting Questionnaire is also based on the theories of Belsky [13–15], Newberger [16] and Baartman [17] and assesses problematic prior history of the parent(s)/caregiver(s) (experience of maltreatment in their own youth or current family; psychological disorders), risk factors of the parent(s)/caregiver(s) (drug and/or alcohol use; negative feelings towards pregnancy; age <19 years of age), risk factors of the child (preterm; low birthweight), risk factors in the social context of the parent(s)/caregiver(s) (single parent; social isolation; low spousal support) and risk factors observed by the Youth Health Care nurse. The main aim of the intervention is to increase parental awareness with regard to the impact of the factors assessed by the Supportive Parenting Questionnaire, on their current daily life and to provide parents with tools to cope with these factors.

The intervention Supportive Parenting consists of six 90 min home visits during the first 18 months after childbirth and focuses on the following elements of parental empowerment: activating social networks, increasing parenting skills and supporting parent(s)/caregiver(s) in getting grip on their own life. A preventive Youth Health Care nurse provides the six home visits of approximately 90 min each. There is one home visit every three months, but according to parents’ needs and preferences there can be more visits during the first months after birth or more visits at the end of the intervention. A home visit consists of a fixed part and a flexible part. During the fixed part the following topics are discussed: handling of/coping with developmental history of the parents, experience of parenthood, expectations with respect to the development of the child, social support and professional support for the family. Additionally during every visit information is given about the different developmental stages of children and the corresponding specific parenting tasks. The flexible part is client-centered. Empowering experiences as well as worrisome experiences are addressed. Parents are asked to come up with ways to improve worrisome aspects of their family-life. The topics of the flexible part are chosen by the parent(s)/caregiver(s) [19]. The intervention is voluntary and parents can indicate to the Youth Health Care nurse if they would like to discontinue the intervention.

The Youth Health Care nurses who provide the home visits have a vast experience in Youth Health Care and have received additional training for the intervention Supportive Parenting. The nurses have the necessary knowledge to provide parent(s)/caregiver(s) with information about health- and development-related issues. However, the nurses are not equipped to provide psychotherapeutic treatment or family therapy and therefore refer to more extensive treatment if deemed necessary [19].

